## Abstract

**Background:**

Postoperative nausea and vomiting after general anesthesia is not only an unpleasant problem affecting 20-30% of surgical patients but may also lead to severe postoperative complications. There is a particularly high incidence of postoperative nausea and vomiting following thyroidectomy. Dexamethasone has been described as highly effective against chemotherapy-induced nausea and vomiting and has been proposed as a first-line method of postoperative nausea and vomiting prophylaxis. Despite this possible beneficial effect, the prophylactic administration of dexamethasone before surgery to prevent or ameliorate postoperative nausea and vomiting has not been established. A bilateral superficial cervical plexus block during thyroid surgery under general anesthesia significantly reduces pain. Of even greater clinical importance, this block prevents the need for postoperative opioids. Therefore, patients undergoing thyroidectomy and a bilateral superficial cervical plexus block are an ideal group to investigate the efficacy of dexamethasone for postoperative nausea and vomiting. These patients have a high incidence of postoperative nausea and vomiting and do not require opioids. They have no abdominal surgery, which can cause nausea and vomiting via a paralytic ileus. Combined with the highly standardized anesthesia protocol in use at our institution, this setting allows all known biases to be controlled.

**Methods/design:**

We will perform a parallel two-arm, randomized (1:1), double-blind, placebo-controlled, single-center trial. Adults (≥18 years) scheduled for primary partial or total thyroidectomy because of a benign disease will be eligible for inclusion. The participants will be randomized to receive a single, intravenous preoperative dose of either 8 mg of dexamethasone in 2 ml saline (treatment group) or saline alone (placebo group). All the patients will receive a bilateral superficial cervical plexus block and standardized anesthesia. The primary outcome will be the incidence of postoperative nausea and vomiting. A total of 152 patients will be recruited, providing 80% power to detect a 50% reduction in the incidence of postoperative nausea and vomiting. Any patients who require opioid treatment will be excluded from the per-protocol analysis.

**Discussion:**

In the present protocol, we reduced bias to the greatest extent possible. Thus, we expect to definitively clarify the efficacy of dexamethasone for postoperative nausea and vomiting prophylaxis.

**Trial registration:**

http://www.clinicaltrials.gov: NCT01189292

## Background

### Scientific background and explanation of rationale

Postoperative nausea and vomiting (PONV) is a common and distressing problem that affects 20-30% of surgical patients after general anesthesia [1]. PONV not only reduces patient comfort but can also lead to serious postsurgical complications, such as dehydration, electrolyte imbalances, the aspiration of the gastric contents, esophageal rupture, suture dehiscence and bleeding [2-9]. Furthermore, PONV significantly affects healthcare costs by prolonging hospital stays [10,11]. In particular, patients undergoing thyroidectomy exhibit a high incidence of PONV, which can be as high as 80% [2,12,13]. PONV after thyroidectomy is most likely caused by edema and inflammation around the neck tissues, leading to evoked parasympathetic impulses through the vagus, recurrent laryngeal and glossopharyngeal nerves to the vomiting center [13-15].

Dexamethasone, a glucocorticosteroid, has been described as highly effective against chemotherapy-induced nausea and vomiting [16,17]. A recently published study comparing the efficacy of six well-established antiemetic strategies concluded that the use of dexamethasone as a first-line method of prophylaxis for PONV is a reasonable treatment option [18]. The exact mechanism by which dexamethasone exerts its antiemetic activity is not well understood. The antagonizing effect of corticosteroids on inflammatory reactions and the dexamethasone-triggered release of endorphins, which results in mood elevation, a sense of well-being and appetite stimulation, may contribute to this effect [19-21]. Due to their anti-inflammatory activity, corticosteroids have been shown to reduce postoperative swelling, pain and sore throat [22-25]. Despite these advantages, the perioperative use of dexamethasone for the prophylaxis and treatment of PONV has not been established [26], possibly due to concerns that the use of corticosteroids would increase susceptibility to infections. However, several studies have indicated that even long-term corticosteroids treatments do not lead to a significant increase in wound infections [27-29]. Another possible reason is the lack of awareness about the antiemetic effect of this type of medication.

Recently, a meta-analysis of five studies that investigated the effects of single-dose dexamethasone application prior to thyroidectomy demonstrated a significant reduction in the relative risk of PONV [30]. However, this meta-analysis was based on studies that did not control for factors potentially influencing PONV, such as postoperative opioid administration or the use of different anesthetics. Two of the five included studies enrolled exclusively Asian women [31,32]. Furthermore, serious doubts about the validity of one of the included studies have been expressed [33]. In summary, the generalizability of this meta-analysis is questionable, and further research is warranted to assess the true efficacy of a single, preoperative dose of dexamethasone for PONV prevention following thyroidectomy.

Recently, our group demonstrated that a bilateral superficial cervical plexus block during thyroid surgery under general anesthesia significantly reduced pain. Of even greater clinical importance, this block prevented the need for postoperative opioids [34,35]. Therefore, patients undergoing thyroidectomy and a bilateral superficial cervical plexus block are an ideal, homogenous cohort in which to investigate the efficacy of dexamethasone for postoperative PONV. These patients exhibit a high incidence of PONV and do not require opioids. They have no abdominal surgery that can cause nausea and vomiting via paralytic ileus. Combined with the highly standardized anesthesia protocol in use at our institution, this setting allows all known biases to be controlled.

### Aim of the study

The objective of the present study is to assess the preventive benefit of a single, preoperative dose of dexamethasone for PONV in patients undergoing thyroidectomy without the postoperative administration of opioids. Additionally, the effects on postoperative pain, hospital stay, wound healing and morbidity will be assessed.

## Methods/design

The study was planned according to the updated Consolidated Standards of Reporting Trials (CONSORT) statement [36] and according to the Declaration of Helsinki, the Guidelines of Good Clinical Practice issued by ICH and the requirements of Swiss regulatory authorities.

### Trial design

This study is a single institution, 1:1 randomized, double-blind, placebo-controlled trial with two parallel arms, comparing a single, preoperative dose of 8 mg dexamethasone (treatment group) with saline (placebo group) in a superiority analysis.

### CONSORT diagram

Figure 1 shows the CONSORT diagram of the trial.

**Figure 1 F1:**
[figure not shown]
CONSORT flow diagram of the trial.

### Eligibility criteria for participants

All the adult patients (aged ≥ 18 years) who are scheduled for a primary partial or total thyroidectomy because of a benign disease at our institution (Kantonsspital St. Gallen, Department of Surgery) will be eligible to participate in the study. The exclusion criteria aim to provide a reliable, balanced and homogeneous study population with high compliance to the study protocol and to avoid adverse effects.“ The inclusion and exclusion criteria are listed below.”

Inclusion criteria:

– Age ≥ 18 years

– Patients scheduled for a partial or total thyroidectomy

Exclusion criteria:

– History of adverse reactions to dexamethasone, propylene glycol or disodium-EDTA

– Chronic pain

– Necessity for sternotomy

– Inability to administer a cervical block (20 ml of 0.5% bupivacaine)

– Diabetes mellitus type 1 or 2 requiring medicamentous treatment

– Pregnancy (tested in all reproductive-age women)

– Glaucoma

– The administration of antiemetic therapy within 48 h before the surgery

– Acute pain requiring analgesics other than acetaminophen or more than a single dose of nonsteroidal anti-inflammatory (NSAID) treatment within 48 h before the surgery

– The use of antipsychotic drugs

– Noncompliance

– Necessity of neck dissection (except compartment C1/level 6)

– Reoperations

### Setting and data collection locations

The patients will be enrolled at the outpatient Clinic of Endocrine Surgery. The participants will be enrolled only by the head of the Clinic of Endocrine Surgery (TC) or under his direct supervision. For each randomized patient, a case report form (CRF) will be generated and updated continuously throughout the hospitalization period. CRFs specifically created for this trial will be used for documentation. All the CRFs are Microsoft Excel-based, and the data will be entered electronically. The CRFs contain extensive probability and range checks to reduce erroneous entries, they are designed to reduce free-text entries to the minimum necessary, and selection from predefined lists (drop-down menus) will be the preferred means of data entry. The completed forms will be printed and signed by the entering physician and then sent to the trial coordinator, along with the data files. The six-week follow-up visits will occur at the outpatient Clinic of Endocrine Surgery.

Several procedures have been designed to enhance the quality of the trial conduct: reviews of the protocol and forms, the direct entry of the data into Excel data entry forms whenever possible, the automatic performance of consistency checks by the electronic data forms, the entry of written or printed data into electronic forms and a review of the data by the trial chair or a delegated person (with the medical content of all the forms reviewed and approved by a monitor).

### Intervention/treatment

Study medication will be prepared by the hospital pharmacy. Medication will be delivered in a syringe containing either 2 ml saline (placebo) or 2 ml saline with 8 mg dexamethasone (Mephameson®, Mepha Pharma, Basel, Switzerland) and are indistinguishable. Syringes will be labeled with the patient’s name, the study name and the study’s patient number.

The anesthesiologist will administer the study medication intravenously 30–60 min before surgery (skin incision) and is completely unaware of the treatment allocation. Thereafter, all the patients will undergo standardized anesthesia, thyroid surgery and routine postoperative care. During the surgery, recurrent laryngeal nerve monitoring will be performed.

A bilateral superficial cervical plexus block will be performed just before the skin incision with a 20-ml syringe and a 20-G × 2^3^/_4_-inch needle (total dose, 20 ml). On each side of the neck, 10 ml of 0.5% bupivacaine solution (Carbostesin® 0.5%; AstraZeneca, Zug, Switzerland) will be administered (total dose, 20 ml) according to the following procedure. On the first side of the neck, along the cranial dorsal edge of the sternocleidomastoid muscle, three deposits of approximately 2.5 ml each will be injected to anesthetize the cervical plexus and its *nervus transversus colli*. To anesthetize the region of the planned skin incision, the remaining 2.5 ml will be injected subcutaneously on each side of the incision. The same procedure will be performed on the opposite side of the neck, using the remaining 10 ml of bupivacaine solution.

The anesthestic technique will be standardized using propofol (Disoprivan® 1%; AstraZeneca) for hypnosis, fentanyl (Sintenyl®, Sintetica, Mendrisio, Switzerland) and remifentanil (Ultiva®;GlaxoSmithKline, Münchenbuchsee, Switzerland) for analgesia, and rocuronium (Esmeron®, MSD, Lucerne, Switzerland) for muscle relaxation.

Propofol will be used as total intravenous anesthesia in a target-controlled infusion (TCI) system according to the Schnider model [37]. Induction will be performed with propofol at an effect-site concentration (Ce) of 4 μg/ml and will be maintained at a Ce of 2–2.5 μg/ml to hold the bispectral index value between 40 and 60. Analgesia will be performed with 0.3-0.4 mg of fentanyl administered intravenously at the beginning of anesthesia. Anaesthesia will be supplemented by remifentanil allowing for stable hemodynamics and avoidance of movements. Remifentanil will be administered in a TCI system according to the Minto model [38], beginning with a Ce of 2–3 ng/ml and increasing to 10–12 ng/ml at the end of anesthesia. Tracheal intubation will be facilitated with intravenous rocuronium at 0.5 mg/kg bodyweight. No further relaxation will be induced because of intraoperative recurrent laryngeal nerve monitoring.

The postoperative first-line therapy for PONV will be intravenous droperidolum (Droperidol®, Sintetica, Mendrisio, Switzerland), with a maximal dose of 3 × 0.5 mg/24 h if the patient’s blood pressure exceeds 120 mmHg. The second-line therapy will be ondansetron (Zofran®, GlaxoSmithKline, Münchenbuchsee, Switzerland) at a dose of 4 mg intravenously.

No routine analgesia is planned. The first-line reserve for pain relief on patient demand will be 1 g of paracetamol (Dafalgan®; Bristol-Myers Squibb, Baar, Switzerland) administered by mouth, with a maximal dose of 3 g/24 h. The second-line reserve will be 1 g of metamizole (Novalgin®; Sanofi-Aventis, Meyrin, Switzerland), with a maximal dose of 4 g/24 h. The third-line reserve will be intravenous morphine (Morphin HCI®, Sintetica, Mendrision, Switzerland); however, its necessity will constitute a protocol violation.

### Outcome measurements

The primary outcome will be the incidence of PONV, which will be assessed at postoperative hours 4, 8, 16, 24, 32 and 48. A patient will be considered to suffer from PONV if nausea or vomiting is documented at any of the postoperative assessments.

One secondary outcome will be the severity of the PONV, measured with a score ranging from 0 to 3 (0 for no nausea; 1 for mild nausea, defined as nausea requiring a single administration of an antiemetic drug; 2 for severe nausea, defined as nausea requiring the repeated administration of antiemetic drugs; and 3 for nausea leading to vomiting).

Other secondary outcomes will be the intensity of pain at rest and under provocation (while rotating the neck 90° to each side), measured at postoperative hours 4, 8, 16, 24, 32 and 48 with a Verbal Rating Scale (VRS) ranging from 0 to 10, with 0 considered to be no pain and 10 considered to be the worst pain imaginable. Additional secondary outcomes will include the length of hospital stay (measured as the number of hours after the intervention), wound healing at the time of discharge and six weeks after the intervention, the amount of anesthetic medication required (total amount of administered fentanyl, remifentanil, rocuronium measured in mg and the total amount of administered remifentanil measured in μg) and postoperative in-hospital morbidity, including wound infection, reoperation, bleeding, prolonged intubation, laryngeal nerve lesion, urinary retention, urinary tract infection, pulmonary infection and gastrointestinal hemorrhage or newly occurring insulin dependence in diabetic patients.

For the safety analysis, adverse events (AEs) and serious adverse events (SAEs) will be evaluated. The patients will be instructed by the investigator to report the occurrence of any AE, defined as an unfavorable and unintended sign, symptom or disease temporally associated with the treatment provided in the present trial. The investigator (treating physician) will be asked to verify the absence or presence of all the AEs predefined on the CRF. Information in the patients’ medical files will be reported using the Common Terminology Criteria for Adverse Events v4.03 (CTCAE 4.03) coding system, rather than a narrative description. AEs will be scored as grade 1 (a mild AE) to grade 5 (death related to the AE), and a causality assessment will be performed.

All grade 4 or 5 AEs will be counted as SAEs, with the exclusion of PONV (as the primary outcome), delayed wound healing (as a secondary outcome) and wound infection (as a secondary outcome). Additionally, postoperative hypoparathyroidism and lesions to the recurrent nerve will not be counted as SAEs because they are considered imminent risks of a thyroidectomy.

The local Ethics Committee and Swissmedic will be informed by the principal investigator about SAEs according to local legislation (VKlin/HMG). A yearly safety summary will be provided to the local Ethics Committee and Swissmedic.

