### Sample size calculation

A sample size determination was conducted for the main outcome variable, the incidence of PONV, using R environment version 13.2 with the gsDesign package. A preliminary retrospective analysis of 100 patients revealed a total incidence of PONV of 48% (unpublished data), confirming previous studies [39]. Based on a power of 0.80 (p = 0.05, two-sided) to detect a 50% reduction in the incidence in PONV (48% vs. 24%) as the clinically relevant treatment advantage between two balanced arms, a total of 123 patients were required for a fixed design. To account for deviations from the expected effect size and incidence due to the avoidance of opioids for postoperative pain relief, a group sequential design was implemented with one interim analysis after 70 patients have completed the study treatment. In a symmetric, two-sided group sequential design with an O’Brien-Flemming alpha spending function [40], the inflation factor was 1.006. The adjusted sample size was estimated to be a total of 124 patients (62 patients per arm). With an assumed rate of 18% protocol violations (derived from a preliminary retrospective analysis of 100 patients), the calculated total sample size was 152 patients (76 patients per arm). To recruit this number of patients, a 30-month inclusion period was anticipated.

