We would like to acknowledge the potential limitations of this study protocol. First, although the scale for PONV measurement has been previously used it is not an explicitly validated scale. Nevertheless, as only patients vomiting or receiving antiemetic medication will be considered to suffer PONV the bias resulting from subjective ratings should be minimal. Second, recent studies suggested that 5-HT3 receptor antagonists might be more effective than dexamethasone in preventing postoperative nausea and vomiting [43]. Nevertheless, in times of constant pressure on health care expenses, the low cost and the general availability of dexamethasone still make it a relevant option for prevention of PONV. Third, although no opioids are applied in the postoperative course they are unavoidable during general anesthesia. Thus it could be possible that differences in operation time might lead to a different amount of applied remifentanil, potentially leading to a bias in PONV. As the study is randomized we consider such a bias very unlikely. However, since we record the amount of applied fentanyl and remifentanil, in case of an imbalance we will be able to adjust for this bias. Fourth, for pain measurement we will use a Verbal Rating Scale ranging from 0 to 10 instead of a 100 mm Visual Analog Scale. At our institution the use of this Verbal Rating Scale for pain measurement during the postoperative course is a common and well established clinical routine. Furthermore, patients are preoperatively informed to rate their pain using the Verbal Rating Scale.

In the present project, we reduced bias as much as possible. Thus, we expect to definitively clarify the efficacy of dexamethasone for PONV prophylaxis. The confirmation of this efficacy by our study will have a major impact because the results may establish dexamethasone administration before thyroidectomy as a new standard in clinical practice. Moreover, the results of this study could be applicable to all types of operations that involve general anesthesia and will stimulate further clinical research in this area.

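### The protocol gives two different rules for a primary-outcome event, and they classify nausea without vomiting or an antiemetic in opposite ways

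*Protocol article*

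**What the plan says.** The Outcome measurements section names the incidence of PONV as the primary outcome, "which will be assessed at postoperative hours 4, 8, 16, 24, 32 and 48", and then states the case rule: "A patient will be considered to suffer from PONV if nausea or vomiting is documented at any of the postoperative assessments". This rule makes no reference to treatment.

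The same section introduces a 0–3 severity score as a secondary outcome. Its bottom two levels are "0 for no nausea" and "1 for mild nausea, defined as nausea requiring a single administration of an antiemetic drug". Level 2 is nausea needing repeated antiemetic doses, and level 3 is nausea leading to vomiting.

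The limitations part of the Discussion, answering the point that the PONV scale is not validated, says: "as only patients vomiting or receiving antiemetic medication will be considered to suffer PONV the bias resulting from subjective ratings should be minimal".

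The Sample size calculation section takes its control rate from the institution's own records, "A preliminary retrospective analysis of 100 patients revealed a total incidence of PONV of 48% (unpublished data"), and is powered "to detect a 50% reduction in the incidence in PONV (48% vs. 24"%). It does not say which case rule produced the 48%.

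**The concern.** Both sentences say when a patient counts as having PONV. One counts any recorded nausea; the other counts only vomiting or a given antiemetic. They disagree about one identifiable group, namely patients with recorded nausea, no vomiting and no antiemetic. The article's own treatment rules allow such patients to exist, because antiemetics are described as therapy for PONV rather than as automatic, and the first-line drug is subject to a blood-pressure condition.

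The event count that enters the chi-square test, at the interim and at the final analysis, is therefore not fixed by the text. The Discussion's reassurance about subjective ratings also depends on the rule that the Methods do not state. If the Methods rule governs, that reassurance loses its basis.

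**Working it through.** **1. The two rules side by side**

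| Patient | Outcome measurements rule | Discussion rule | 0–3 score |
|---|---|---|---|
| No nausea, no vomiting, no antiemetic | no event | no event | 0 |
| Nausea, antiemetic given, no vomiting | event | event | 1 or 2 |
| Nausea leading to vomiting | event | event | 3 |
| Nausea, no vomiting, no antiemetic | **event** | **no event** | **no level fits** |

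The whole discrepancy lies in the last row.

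**2. The plan's own sample size**

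Inputs from the Sample size calculation section: 48% vs 24%, two-sided alpha 0.05, power 0.80, 1:1 allocation. With the pooled-variance formula and no continuity correction:

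- mean rate = (0.48 + 0.24)/2 = 0.36
- n per arm = [1.960 × √(2 × 0.36 × 0.64) + 0.842 × √(0.48 × 0.52 + 0.24 × 0.76)]² / 0.24² = 61.6, so 123.2 in total (stated: 123)
- 123.2 × 1.006 = 123.9 (stated: 124)
- 124/0.82 = 151.2, rounded up to an even 152 (stated: 152)

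The stated figures reproduce, so the arithmetic is not at fault.

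**3. Can the choice of rule change the primary conclusion?**

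This is a hypothetical illustration at 76 per arm, using the uncorrected chi-square and the final alpha of 0.0488 from the Statistical analysis section.

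- Any documented nausea or vomiting, 36 vs 24 events: χ² = 152 × (36 × 52 − 24 × 40)² / (76 × 76 × 60 × 92) = 3.97, p = 0.046, significant.
- Suppose 6 and 4 of those events were untreated nausea only. Then 30 vs 20 events: χ² = 152 × (30 × 56 − 20 × 46)² / (76 × 76 × 50 × 102) = 2.98, p = 0.084, not significant.

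**4. Effect on power**

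The documents give no rate of untreated nausea, so every rate below is an assumption. For control rate c, treated rate t, m = (c + t)/2, n per arm and alpha 0.0488 (z = 1.970):

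power = Φ{ [|c − t| − 1.970 √(2m(1 − m)/n)] / √([c(1 − c) + t(1 − t)]/n) }

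At 48% vs 24% this gives 80.0% with 62 per arm and 87.5% with 76 per arm.

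*Case A: the 48% is the vomiting-or-treated rate and the Methods rule is used.* Let a share u of the remaining control patients have untreated nausea, so c = 0.48 + 0.52u. Power at 62 per arm:

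| Assumption about the treated arm | u = 10% (c = 53%) | u = 20% (c = 58%) | u = 30% (c = 64%) |
|---|---|---|---|
| No drug effect on untreated nausea, t = 0.24 + 0.76u | 68% | 57% | 46% |
| 24-point difference kept, t = c − 0.24 | 78% | 77% | 77% |
| u halved by the drug, t = 0.24 + 0.38u | 83% | 86% | 89% |
| 50% relative reduction kept, t = c/2 | 86% | 91% | 95% |

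*Case B: the 48% is the any-nausea rate and the Discussion rule is used.* A share s of those cases drops out and the 50% relative reduction is kept. For s = 10%, 20%, 30% and 40%, power at 62 per arm is 73%, 66%, 57% and 49%.

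*Case C: the 48% already follows the rule that is used.* Power is unchanged at 80%.

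**The case against.** The strongest reply is that the two rules coincide in practice. The Discussion's limitation concerns the scale by which PONV is measured, which suggests that the 0–3 score is the recording instrument. Every non-zero value on that score implies an antiemetic or vomiting. If nausea is documented only through the score, the Discussion merely explains how the Methods rule is recorded. One can add that a Methods definition ordinarily outranks a remark in a Discussion.

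Part of this stands: the reading is possible, so it is not established that real patients will be classified differently. It does not remove the problem. Outcome measurements presents the score as a secondary outcome and defines the primary event separately. On the single-instrument reading, a patient with untreated nausea would have to be entered as having none, against the score's own wording. If the Methods rule simply prevails, the Discussion's argument about rating bias is wrong.

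A reader might go further and infer that the trial is underpowered, quoting the 68%, 57% and 46%. The documents do not support that. Those values assume that dexamethasone has no effect on untreated nausea; other assumptions, no better or worse supported, leave power roughly level or raise it.

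A reader might also infer that the severity analysis changes with the primary rule. It does not: the score is defined on its own and is the same under either rule. Its missing level is a separate defect.

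Nor do the documents show that the rule would be chosen after seeing results. A full protocol or analysis plan that is not shown may settle it.

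**Conclusion.** The contradiction is real and concerns the definition of the primary event. It is a statement made twice in different terms, rather than detail left to a fuller document. It affects patients with documented nausea, no vomiting and no antiemetic, and the worked example shows that such patients can be enough to move the result across the significance threshold. That example is hypothetical.

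The size of the effect cannot be derived from the documents. With untreated nausea assumed in 10–30% of otherwise event-free control patients, power at 62 per arm runs from about 46% to 95% depending on the drug's effect on such nausea. It is 80% if the 48% already used the chosen rule. Neither a loss nor a gain in power can be claimed. The gap in the severity score stands as a second, independent defect in a secondary outcome.

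**What to change.** Before any unblinded look at the data:

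- Reconcile the Outcome measurements section and the Discussion to one primary event definition. The simplest route is to keep the Methods definition and correct the Discussion sentence, including its claim that bias from subjective ratings is minimal.
- Analyse the other definition as a named sensitivity analysis.
- State how nausea without an antiemetic is scored on the 0–3 scale, including for patients already enrolled.
- Confirm that the 48% planning rate uses the chosen definition, and restate the power if it does not.

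The cost is mostly wording. Recruitment began in October 2011 and is ongoing, so a new score level, if one is added, may not be available for patients already scored, and the plan must say how they are handled. The stated power may become less favourable.
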